### Blinding

Due to the nature of the dietary intervention, neither the participants nor the research staff responsible for carrying out the intervention were blinded to the intervention allocation. Only the study staff responsible for data collection, sample processing, and analysis were blinded.

### Intervention

During the intervention, participants received an omnivorous diet that varied in the quantity and nutritional quality of plant foods according to their assigned arm: (1) low proportion of healthful plant foods (LH), (2) medium proportion of healthful plant foods (MH), (3) high proportion of healthful plant foods (HH), or (4) high proportion of unhealthful plant foods (HU). The intervention HH served as the control, as the diet implemented here comes closest to the intake of plant foods recommended by international dietary guidelines (eg, the “healthy reference diet” proposed by the EAT-*Lancet* Commission on Healthy Diets from Sustainable Food Systems [40]).

The intervention arms were designed to mimic dietary patterns similar to those described by the original plant-based diet indices [1]. To better reflect European eating habits, slight adjustments were made to the categorization of plant foods as healthful or unhealthful, and plant-based alternatives were included. Whole grains, fruits, vegetables, legumes, nuts, vegetable oils, tea, and coffee were categorized as healthful. Refined grains, fried potato products, fruit juices, sugar-sweetened beverages, sweets, and desserts were categorized as unhealthful. As literature on the nutritional quality of potatoes does not distinguish between different preparation methods, there is a lack of evidence to classify cooked, baked, or roasted potatoes as healthful or unhealthful. For this reason, this food group was categorized as “neutral.” Plant-based alternatives were also classified as neutral due to their heterogeneous nature and inconsistent evidence on health associations. Animal-based foods were also viewed as neutral, and no BFI candidates for animal food were considered for the intended biomarker analysis.

For this study, a total of 35 base menu plans with an average energy content of 2000 (SD 50) kcal were calculated with the software PRODI (version 7.2, Nutri-Science GmbH). These base menu plans were later energy-adjusted to create the menu plans for the participants as described in the following section. Each menu plan consisted of 4 meals. In total, 7 menu plans were calculated for the run-in period and 7 for each intervention arm. During both intervention weeks, the same 7 daily menu plans were used. However, the sequence of these menu plans differed between the first and the second week, resulting in a variation in the foods consumed in relation to the sampling times. This should help to test whether the MBP is robust and can correctly assign participants to their intervention based on the overall dietary pattern, rather than by single dishes.

The main metric used to calculate the menu plans was the proportion of plant food servings while adhering as closely as possible to a macronutrient ratio of 50/30/20 energy percent for carbohydrates/fat/protein. Table 1 shows the average proportions of plant foods in the final menu plans of the run-in period and the 4 arms during the intervention. The base menu plans and the definition of serving sizes can be found in Multimedia Appendix 1.

**Table 1. T1:** Proportions of plant foods in the calculated menu plans. Proportions of plant foods (in %) in the diet of the run-in and the 4 arms during the intervention by the metrics of servings, weight, and calories.

Metrics	Run-in	LH^a^	MH^b^	HH^c^	HU^d^
Proportion of plant foods of total servings (in %)	39	43	62	84	82
Proportion of plant foods of total weight (in %)	51	47	61	86	79
Proportion of plant foods of total calories (in %)	50	50	67	87	85

a LH: low proportion of healthful plant foods.

b MH: medium proportion of healthful plant foods.

c HH: high proportion of healthful plant foods.

d HU: high proportion of unhealthful plant foods.

For each meal, a time window for consumption was defined: breakfast (6 AM to 10 AM), lunch (11:30 AM to 2:30 PM), snack (10 AM to 5 PM), and dinner (5 PM to 8:30 PM). Alcohol, extra sugar, and dietary supplements were prohibited, while coffee, black tea, and green tea were limited to a total of two cups (=300 mL) per day. All participants could freely consume 100 mL of cow milk daily to add to coffee or tea.

Prior to each of the 5 study waves, the base menu plans were individually energy-adjusted to the calculated total energy expenditure (TEE) of each participant (see the following section), and the corresponding recipes were created. If the given portion sizes were too large, the participants were allowed to reduce the amounts of ingredients evenly to maintain the proportion of plant foods. In this case, they had to weigh back the leftover food. For this purpose, all participants were provided with kitchen scales from the same manufacturer in order to ensure comparability. If the participants were still hungry, they could eat an additional snack consisting of white bread and cream cheese, with low impact on plant biomarkers. Any other modifications to the intervention were prohibited.

Participants prepared and consumed meals and collected urine and stool samples at home, carrying out the intervention as part of their daily life. For this purpose, the study center fully supplied them with all the necessary food in the required quantities and provided them with printed and digital recipe folders containing all the information, instructions, recipes, and daily logs. All recipes included a list of the individual energy-adjusted values of the ingredients and step-by-step instructions on how to cook or prepare the meals. The daily logs had to be completed during the run-in and the intervention. Here, participants were asked to record the exact time they ate each meal, the amount and type of tea or coffee they drank, and how much of the additional snack, if any, they consumed. There was also space for notes, mostly about permitted deviations from the recipes, such as the exact amount of food that was not eaten and weighed back.

Participants were closely monitored throughout the study. Personal contact was the main mode of communication, with 2 contacts per week (visits to the study center and food deliveries to the participants’ homes) as well as the possibility of contacting the study center by email on weekdays or the study hotline (SMS text message and phone call) at any time.

### Energy Adjustment

The menu plans were linearly energy-adjusted using Excel (Microsoft Corp) to create the individual menu plans for the participants. Total energy expenditure (TEE, in kcal) of each participant (see section Total Energy Expenditure Calculation) divided by the total kcal of the base menu plan yields a factor. This factor was then multiplied with the weight (in grams) of each food item in the base menu plan so that the plant proportions and macronutrient ratios are not altered. Resulting values ≤10 were mathematically rounded in increments of 1; values >10 in increments of 5; values >50 in increments of 10. The food items pretzel rolls (frozen), pretzels (frozen), schnitzel (vegan and pork, frozen), eggs, and crispbread were rounded to whole pieces. Wraps, bread rolls, and bagels were rounded to 0.5 piece increments.

### Food Logistics

Food purchase, preparation of food packages, and delivery to the participants were carried out based on the energy-adjusted menu plans by the study center staff. Food was purchased at wholesale markets and supermarkets. The selection of food items remained the same for each of the 5 waves and was not adapted to the seasons. Food items that are not available year-round, such as strawberries, were only used frozen.

All shelf-stable foods were delivered to participants before the first study day. Frozen foods were delivered once a week. Fruits, vegetables, and refrigerated foods (dairy and meat products) were supplied twice a week, at the visit to the study center and via home delivery.

### Anthropometry and Body Composition Assessment

Anthropometric data were assessed at all visits using standard methods. Measurements were taken in underwear, without shoes. Waist and hip circumferences were measured to the nearest 0.1 cm using the ergonomic measuring tape seca 201 (seca GmbH & Co KG). Three measurements were taken for each circumference, and the averages were recorded for analysis. Body composition was assessed by bioelectrical impedance analysis (BIA) using the seca mBCA 515. Body weight was measured to the nearest 0.05 kg, also using the seca mBCA 515, and height was measured to the nearest 0.01 m, using the seca 285 height measuring device. Weight and height were used to calculate the respective BMI (in kg/m²).

### Total Energy Expenditure Calculation

The TEE was calculated to enable adjustment of the menu plans to the individual energy requirements of each participant. To determine the TEE, resting energy expenditure (REE) and activity energy expenditure (AEE) were calculated. For REE calculation, the fat-free mass (FFM), which was determined as part of the BIA measurement, was used in the formula of Armbruster et al [41]:

REE (kcal) = 21.14 × FFM (kg) + 345.5

The AEE was determined using accelerometers (move 4, movisens GmbH). The accelerometers were placed on the participants’ hips at the screening visit and were then worn for 1 week. The software *SensorManager* (version 1.16.1, movisens GmbH) was used to program the sensor and read out the acquired data, and the software *DataAnalyzer* (version 1.15.1, movisens GmbH) was used to analyze the data and calculate the required parameters.

The participants’ TEE was calculated with the estimated REE, the AEE measured by accelerometry, and the diet-induced thermogenesis (DIT), which is assumed as 10% of the sum of REE and AEE [42]:

TEE (kcal) = REE (kcal) + AEE (kcal) + DIT (kcal)

### Habitual Diet Assessment (30-Day Food Frequency Questionnaire)

The validated 57-item FFQ applied in the German Health Interview and Examination Survey for Adults 2008-2011 (DEGS) of the Robert Koch-Institut was used to assess the habitual diet of the participants [9]. The FFQ includes questions about the frequency of consumption and usual portion sizes of different food groups consumed by the participants in the 4 weeks prior to study entry. The questionnaire was given and explained to the participants at visit 1 at the study center, with the request to complete it at home and return it at visit 2.

### Urine and Blood Samples for Biomarker Analysis

#### Analytical Method

During the study, several urine and blood samples were collected to measure BFIs by liquid chromatography-mass spectrometry (LC-MS). The LC-MS method is being developed independently of the PLAENTI study in the Plant*Intake* project. It aims to quantitatively analyze the BFIs described in the list of biomarkers that can be found in Multimedia Appendix 2. The samples of PLAENTI will be analyzed using the finalized analytical method.

#### Blood Samples

Blood samples were collected at every visit after at least 10 hours of fasting. Participants were placed on an examination couch in the supine position. After cutaneous disinfection, a tourniquet was moderately applied (safety blood collection device: Venofix Safety, B. Braun SE), and blood samples were taken from an antecubital vein by experienced medical study staff. Blood was drawn into ethylenediaminetetraacetic acid (EDTA)- or lithium-heparin-containing S-Monovette tubes (Sarstedt AG & Co KG) for plasma collection and into anticoagulant-containing serum-gel S-Monovette tubes (Sarstedt AG & Co KG) for serum collection.

After venipuncture, the filled tubes for plasma preparation were immediately centrifuged (20 °C, 10 minutes, 2500× *g*, Heraeus Multifuge X3R, Thermo Fisher Scientific) and kept on ice until aliquoted into microtubes. Erythrocytes (from lithium-heparin tubes) were washed with 0.9% sodium chloride solution and pipetted into CryoPure tubes (Sarstedt AG & Co KG). Tubes for serum preparation were allowed to clot for 30 minutes at room temperature, then centrifuged (20°C, 10 minutes, 2500×*g*) and kept on ice until aliquoted into microtubes or CryoPure tubes. Microtubes containing EDTA plasma, lithium-heparin-plasma, or serum were frozen at −20°C and then stored at −70°C until analysis. CryoPure tubes containing erythrocytes or serum for long-term storage were frozen at −20°C and then stored in the cryogenic storage tanks at −194°C.

#### Urine Samples

For urine sampling, participants received detailed oral instructions from trained study staff and a folder with written manuals for the collection procedures, including a calendar of sampling times. They were also given a log to record the exact time of sampling, any difficulties, and, for females, whether they were menstruating.

The 24-hour urine samples were collected from the morning before until the morning of visits 2, 3, 4, and 5. Participants were asked to start the urine collection after their first morning void, which was collected as a morning spot urine sample. Participants were provided with 3 urine collection containers (2 L capacity each, Sarstedt AG & Co KG) and cool bags with thermal packs. During collection, participants were asked to store their urine at home in the refrigerator or in a cool bag with the prechilled thermal packs to keep the collected urine permanently cool. This cool bag was also used to ensure the chilled transport of the collected urine to the study center on visit days. At the study center, the volume of the collected 24-hour urine was determined. The urine was mixed, and 15 mL of it was pipetted into a tube, centrifuged (4 °C, 10 minutes, 2500× *g*), and kept on ice until aliquoted into microtubes or CryoPure tubes. Microtubes containing 24-hour urine were frozen at −20°C and then stored at −70°C until analysis. CryoPure tubes for long-term storage of aliquots were frozen at −20°C and then stored in cryogenic storage tanks at −194°C.

Spot urine samples were collected from participants at home the evening and morning before the start of the 24-hour urine collection. Additional spot urine samples were collected halfway through each intervention week, also in the evening and the following morning (see Figure 1). The evening sample had to be the last urine before going to bed, and the morning sample had to be the first morning void. Spot urine samples were collected in 100 mL polypropylene collection cups with an integrated transfer unit in the screw caps and directly transferred to 10 mL vacuum tubes (V-Monovette, Sarstedt AG & Co KG). Participants were asked to store the filled vacuum tubes in the refrigerator immediately after sampling. A cool bag with prechilled thermal packs was used to transport the samples to the study center. At the study center, the vacuum tubes were centrifuged (4°C, 10 minutes, 2500× *g*) and kept on ice until aliquoted into microtubes or CryoPure tubes. Microtubes containing spot urine were frozen at −20°C and then stored at −70°C until analysis. CryoPure tubes for long-term storage of aliquots were frozen at −20°C and then stored in cryogenic storage tanks at −194°C.

### Stool Samples

The collection of stool samples was optional for participants. Their willingness to provide a stool sample was queried at the screening visit. Participants who agreed to provide stool samples were given detailed oral instructions and a written manual on the sampling procedure and were provided with stool collection kits containing a fecal sample collection aid (servoprax GmbH), a collection cup (Sarstedt AG & Co KG), a disposable spatula, and a 60 mL twist-seal bag (VWR International GmbH), as well as a thermal pack for transport, gloves, and zip-log bags for packaging. Participants collected two cherry-sized stool samples (approximately 5 g) on different days in a 72-hour window before visit 1 and visit 4, and one cherry-sized stool sample in a 48-hour window before visit 2 and visit 5. Samples were frozen at −20°C immediately after collection at the participants’ home, delivered frozen to the study center, and then stored at −70 °C until aliquoted. Samples were thawed and manually mixed inside the collection bags before taking aliquots of approximately 500 mg each for further processing. Aliquots were frozen immediately at −70°C until further analysis.

Participants who collected stool samples also completed a short questionnaire on gastrointestinal symptoms at visits 1, 2, 4, and 5, concerning the previous week or 2 weeks, respectively. The questionnaire covers stool frequency as well as the occurrence and frequency of the following symptoms: abdominal pain, heartburn, burping, watery stool or diarrhea, lumpy or hard stool, constipation, feeling full after food intake, gastrointestinal sounds, flatulence, nausea, and increased or decreased hunger or appetite.

Stool samples were collected for exploratory analyses. First, we can examine the effects of different quantities and qualities of plant foods on the gut microbiota. Another approach that can complement PLAENTI is to detect plant taxa in stool samples by genetic analysis, as described by Petrone et al [43].

### Compliance

Care was taken to ensure that only the most conscientious individuals were included in an attempt to keep the dropout rate as low as possible. During the telephone screening and the information session at the screening visit, potential participants were given detailed information about the study procedure and, in particular, the effort required to take part in the study. In addition to the inclusion and exclusion criteria, potential participants were asked about other issues such as food aversions, usual eating habits, and the compatibility of their daily routine with participation.

To improve participants’ compliance during the ongoing study, a number of measures were taken. As detailed in the “Intervention” subsection, food consumption was monitored using daily logs. Participants had to record their exact mealtimes, as well as the exact amount of uneaten food, in these daily logs. There was also a urine collection log to document the time of sampling. There was very close personal contact between the study staff and the participants during the weekly visits and food deliveries. In addition, the team of the study center was always available by email or telephone to directly respond to any questions or concerns that participants might have and to provide them with optimum support. Noncompliance occurred when relevant samples were missing, instructions regarding the intervention were not followed, or medical events (medication, illness) conflicted with participation. Noncompliance led to exclusion.

### Adverse Events

Safety monitoring included the recording, assessment, and follow-up of adverse events and the determination of the following safety parameters in blood at the first and last visit: gamma glutamyl transferase, glutamic oxaloacetic transaminase, bilirubin (total), creatinine, uric acid, glucose, triglycerides, and total cholesterol (all in serum), and a blood count. Only commercially available food was used, which was fully provided by the study center. Allergies to any food or food ingredient in the study diet were assessed in advance and resulted in exclusion (see Textbox 1). Therefore, no serious adverse events related to the consumption of the intervention diet were expected. Participants with unacceptable adverse events or acute illnesses that interfered with study participation were excluded from the study. This decision was made individually by the study physicians.

### Statistics

#### Outcomes

The primary outcome of the study is an MBP measured in urine and blood samples from participants in the arms LH, MH, and HH at defined time points during the 2-week intervention period. The analysis metric for the primary outcome is the change in levels of biomarkers contained in the MBP from visit 2 to visit 4, considered as a combined panel value. The variables will be aggregated and described by average values and SDs.

The secondary outcome is the MBP measured in urine and blood samples at defined time points in the two arms, HH and HU. The analysis metric for the secondary outcome is also the change in levels of biomarkers contained in the MBP from visit 2 to visit 4, considered as a combined panel value. The variables will be aggregated and described by average values and SDs.

Moreover, the comparability of the biomarker levels in the different types of urine samples (24-hour urine, spot urine, and pooled spot urine) will be investigated to gain insight into the applicability of spot urine sampling in epidemiological studies. Other outcomes of an exploratory nature will also be measured. Metabolomic analyses will be performed by measuring different classes of metabolites in the urine and blood samples. For microbiome parameters, the analysis metrics are alpha diversity (number and uniformity of species distribution within a microbiome), beta diversity (dissimilarity of the composition of different microbiomes), and abundance of individual taxa in different microbiomes. The results of the FFQ will be used to characterize the participants’ habitual diet.

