The aim of the PLAENTI study is to validate an MBP for the assessment of the quantity and nutritional quality of plant foods in an omnivorous diet. Accordingly, the primary objective of the validation study PLAENTI is to test whether the quantity of plant foods within the diet can be correctly estimated by measuring levels of selected urinary and blood biomarkers that are part of the MBP. A secondary objective is to test whether a difference in nutritional quality (healthful vs unhealthful) of plant foods in the diet can also be detected with the MBP. The effect of potential confounders (age, sex, physical activity, and body composition) on the precision of estimating plant food intake using the MBP will be assessed. Finally, the MBP will be determined in both 24-hour urine and spot urine samples. This will allow a comparison of the different sample types (24-hour urine collection, evening and morning spot urine, and different pools of these spot urines) to assess their reliability in reflecting dietary patterns through biomarker analysis. To address these objectives, participants received a 2-week dietary intervention with different proportions and nutritional qualities of plant foods, while urine and blood samples were collected at several time points.

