#### Statistical Methods

The aim of the primary statistical analysis is to detect a trend in the MBP as a function of the proportion of healthful plant foods consumed by the participants. Here, the values of the MBP determined at visit 4 are adjusted with the baseline values from visit 2. The MBP values are compared between the interventions using the Williams test. The comparison is made for the 3 diets with different proportions of healthful plant foods (low, medium, or high). For simplicity, it is assumed that the primary outcome is normally distributed and has a homogeneous variance. The statistical hypothesis is that the primary outcome will follow a trend for the ordered categories of low, medium, and high intake of healthful plant foods. Group HH, with a high proportion of healthful plant foods in the diet, serves as a control. The following 3 average values of the MBP are assumed for the 3 intervention groups: *μ*1*, μ*2*,* and *μ*3. All intervention groups have a comparable sample size. An average different response is expected in the group with low and medium consumption compared to the high consumption (control) of healthful plant foods. The global null hypothesis is formulated as *H*0*: μ*1*=μ*2*=μ*3 versus the alternative hypothesis *H*1*: μ*3*≥μ*2*≥μ*1, with at least one strict inequality. When modeling the MBP, adjustment is made for the following potential confounding variables: age, sex, body composition (assessed by BIA), and physical activity (assessed by accelerometry). The MBP is considered to be validated if a significant monotonic trend is observed (*P*<.05).

As the main secondary analysis, mean MBP values will be compared between the HH and HU intervention arms, characterized by similar proportions of plant foods but differing in nutritional quality (healthful vs unhealthful). Group differences will first be assessed using an independent-samples *t* test, followed by linear regression models incorporating the same set of adjusting variables.

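### The validation rule uses only LH, MH and HH, so it cannot tell a panel that measures plant-food quantity from one that reads healthful plant foods only

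*Protocol article*

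**What the plan says.** All references are to the protocol article.

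- **Objective.** The closing paragraph of the Introduction says the primary objective is to "test whether the quantity of plant foods within the diet can be correctly estimated" from urinary and blood biomarkers. Nutritional quality, healthful against unhealthful, is a separate secondary objective.
- **Primary outcome.** Outcomes: "The primary outcome of the study is an MBP measured in urine and blood samples from participants in the arms LH, MH, and HH". The metric is the visit 2 to visit 4 change, expressed as a combined panel value.
- **Primary test.** Statistical Methods gives the aim as "to detect a trend in the MBP as a function of the proportion of healthful plant foods consumed by the participants", assessed with a Williams test on the ordered means of the three arms.
- **Decision rule.** The same section: "The MBP is considered to be validated if a significant monotonic trend is observed", at P<.05. It sets no condition on HU.
- **Use of HU.** HU is compared with HH as the main secondary analysis. The metric is again the visit 2 to visit 4 change as a combined panel value.
- **Arms.** Table 1 gives total plant share of servings as LH 43%, MH 62%, HH 84% and HU 82%. The Discussion (Study Design) says that up to 10% of HU servings were fresh fruit and vegetables.

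**The concern.** The objective names all plant foods, while the test and the decision rule concern healthful ones. In the three arms used, the two quantities put the diets in the same order. A significant trend is therefore equally consistent with a panel that tracks total plant intake and with one that responds only to whole grains, fruit, vegetables, legumes and similar foods.

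The distinction matters to later users. If a panel that responds only to healthful foods is released as a measure of plant-food quantity, it will understate intake in people whose plant foods are mostly refined grains, juices, sweets and fried potato products. The trial includes an arm that could detect this, but the rule does not consult it.

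**Working it through.** **1. Order of the arms (Table 1, % plant)**

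| Metric | LH | MH | HH | HU |
|---|---|---|---|---|
| Servings | 43 | 62 | 84 | 82 |
| Weight | 47 | 61 | 86 | 79 |
| Calories | 50 | 67 | 87 | 85 |

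On every metric LH < MH < HH, the same order as the low, medium and high healthful labels. HU lies near HH on quantity (gaps of 2, 7 and 2 points) and well above LH (39, 32 and 35 points).

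**2. What each kind of panel predicts**

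- Quantity panel: LH < MH < HH, with HU close to HH. Linear interpolation on the plan's assumed means puts HU at 3.8 − 1.8 × (84 − 82)/(84 − 62) = 3.64.
- Healthful-only panel: LH < MH < HH, with HU low.

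The predictions differ only in HU. The Williams statistic contains no HU term, so its chance of success is the same for both panels.

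**3. The plan's own power figure**

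Inputs from Sample Size: n = 15 per arm, means 1, 2 and 3.8, a variance of 2.5, and a stated power of 0.81. I simulated the Williams multiple-contrast t test with pooled variance on 42 df and a critical value of about 2.20 (two-sided 0.05). The contrasts were (−1, 0, 1) with (−1, ½, ½) for LH as base, or with (−½, −½, 1) for HH as base.

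- Variance 2.5 as printed (SD 1.58): power 0.996 (LH base) or 0.997 (HH base).
- SD 2.5: power 0.814 (LH base) or 0.844 (HH base).

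Of these two readings, only SD 2.5 reproduces 0.81. That is a separate matter, so both are carried forward.

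**4. Adding a requirement that HU exceed LH (illustration)**

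The article gives no HU mean, so three values are assumed: HU = 1 (read as LH), 2 (read as MH) and 3.8 (read as HH). The added test is a two-sample t test at one-sided 0.025 with 15 per arm. Its noncentrality is (HU − 1)/(SD × √(2/15)). The standard error is 0.913 for SD 2.5 and 0.577 for variance 2.5. For HU = 2 the noncentrality is 1.10 or 1.73; for HU = 3.8 it is 3.07 or 4.85.

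| Assumed HU mean | Current rule, SD 2.5 | Current rule, variance 2.5 | With HU>LH, SD 2.5 | With HU>LH, variance 2.5 |
|---|---|---|---|---|
| 1 | 0.81–0.84 | >0.99 | 0.025 | 0.025 |
| 2 | 0.81–0.84 | >0.99 | 0.18 | 0.39 |
| 3.8 | 0.81–0.84 | >0.99 | 0.73–0.74 | 0.99 |

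In the first row, 0.025 is simply the level of the added test, because HU = LH is its null hypothesis. The second row shows the limit of that test: a panel that reads HU as MH still passes fairly often.

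**5. Precision of the supporting intervals**

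The half-width of a 95% interval for HU-MH or HU-HH is about 2.048 × SD × √(2/15), which is 1.87 for SD 2.5 and 1.18 for variance 2.5. The assumed MH-HH gap is 1.8. If the SD is 2.5, the intervals will only roughly place HU between MH and HH. These calculations leave out the planned covariate adjustment and the loss of one participant in LH (14 completed).

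**The case against.** - **The design varies one thing at a time.** Amount changes across LH, MH and HH; type changes between HH and HU at nearly matched amount. The hypothesis is openly worded as healthful plant foods. This is a fair reading of the design, and it limits the point to a mismatch between the objective and the rule. It does not support a quantity claim for diets high in unhealthful plant foods.
- **HU is not discarded.** It is the main secondary arm, and its mean and SD will be reported, so a low HU value would be visible. That stands. But the rule lets nothing seen there overturn the validation, and the secondary analysis treats an HH-HU difference as a finding on quality.
- **The panel may have separate scores.** It was still to be developed, and the article speaks of a combined panel value for each outcome without saying that the weights are identical. So it cannot be asserted that success on the secondary test contradicts the quantity claim. That follows only if one score serves both objectives: quantity then predicts HH about equal to HU, and quality predicts a difference.
- **Full confounding.** A reader might infer that quantity and healthfulness are fully confounded in the primary analysis. The documents support only identical ordering. The healthful and unhealthful split within LH, MH and HH is not tabulated in the article.
- **A fixed false-validation rate.** A reader might also take 0.81 to 0.84 as the probability that a wrong panel will be validated. It is the power of the trend test under assumed means, conditional on the panel being of that kind. HU = LH is an extreme case, and HU contains some fresh fruit and vegetables.

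**Conclusion.** The mismatch holds. The stated objective is quantity of plant foods, and the stated rule can establish only a trend over diets ordered in the same way by total and by healthful plant foods. This follows from the arm definitions, Table 1 and the decision rule, and needs no simulation. The probabilities illustrate its size under an assumed HU mean and two readings of the printed 2.5.

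The point should be fixed, but it is not fatal. No randomised comparison is invalidated, and rewording the claim is a full remedy. A stronger conclusion, that the trial would pass a panel known to misread HU, is not supported: the article gives neither an HU mean nor a scoring rule.

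**What to change.** Choose one route, and date the change before MBP values are seen by arm:

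- **(a) Narrow the claim.** Reword the primary objective and the conclusion to the quantity of healthful plant foods. The analysis stays as planned. The cost is that a trend result no longer supports a statement about plant foods in general.
- **(b) Keep the general quantity claim and bring HU into its criterion.** Require HU above LH on the quantity score in addition to the trend, and report HU-MH and HU-HH with 95% confidence intervals. The intervals are needed because HU above LH alone does not exclude a panel that reads HU as MH.

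If (b) is chosen, also state whether the HH-HU quality comparison uses the quantity score or a separate one. If there is one score, say how an HH-HU difference will be interpreted for quantity.

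Both routes are changes of wording. Fifteen HU participants completed the study, their samples are stored, and the article describes the biomarker analysis as still to come. Under (b), the chance that a genuine quantity panel (HU = 3.8) meets the whole criterion falls from 0.81–0.84 to 0.73–0.74 if the SD is 2.5. It stays at about 0.99 if the variance is 2.5.
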